#### Analyses of primary aims

Imbalances in key stratification variables in baseline data that were not addressed via randomization will be adjusted for in the analyses of treatment effects. Analysis of variance and chi-square tests will be employed to identify those baseline differences on prognostic variables, like age discordance and couple HIV status, the main study outcomes, and demographic variables.

Cochran-Mantel–Haenszel tests of two independent binomial proportions will be used to detect differences in the STI prevalence rates, our primary biological outcome, from baseline to 12-month follow-up. Our main behavioral outcome is condomless anal sex with serodiscordant or unknown status partners. In order to account for the nested nature of dyadic data, we will assess outcome, as well as our secondary outcomes, with multilevel latent growth modeling. Data from all four of our follow-up surveys (3, 6, 9, and 12 months) will be incorporated into those growth models. The treatment condition will be used as a dyad-level predictor within the multilevel framework that will predict differences in intercept and slope terms. This method will not only detect differences in change over time by the treatment condition predicting slopes, but we will also detect differences at each follow-up time point by shifting the intercepts from 3-month to 6-, 9-, and 12-month follow-up.

Indicators of relationship functioning will be tested as mediators of significant differences between the two study arms on the primary outcomes. We will employ Fritz’s [56] approach for testing longitudinal mediation in latent growth models. This is a parallel process approach where the mediator is treated as a lagged effect to maintain the temporal order of events between the mediator and the outcome. A percentile bootstrap test will be used to determine the indirect effect of treatment on the outcome through the lagged mediator.

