### Trial objectives and hypotheses

The goal of the current study is to conduct an attention-matched randomized controlled trial (RCT) with a 12-month follow-up to assess the efficacy of 2GETHER in reducing HIV risk relative to a positive affect enhancement program for couples. We are recruiting a sample of young male couples living in Chicago and surrounding areas, who will complete intervention sessions face-to-face in a university setting. We make the following specific hypotheses:

H1: For our primary outcomes, we will observe greater reductions in indicators of HIV risk at 12 months post-intervention among participants randomized to 2GETHER relative to control, including reductions in (1) self-reported condomless anal sex with serodiscordant or unknown status partners and (2) urethral and rectal Chlamydia and Gonorrhea infections. In addition to these primary outcomes measured at the individual level, we anticipate significant improvement in self-reported partner relationship agreement concordance and reductions in the frequency of agreement breaks in 2GETHER relative to control. Finally, we hypothesize that indicators of relationship functioning (e.g., communication, satisfaction) will mediate intervention effects.

H2: With regard to secondary and exploratory outcomes, we will observe greater improvements in various aspects of the HIV continua of prevention and care at 12 months post-intervention among participants randomized to 2GETHER relative to control. For secondary outcomes, we expect to observe improvements in HIV testing uptake (among HIV-negative and unknown status participants) and antiretroviral medication adherence (among HIV-positive participants). Exploratory outcomes will be the uptake of and adherence to pre-exposure prophylaxis (PrEP) among HIV-negative and unknown status participants and reductions in viral load among HIV-positive participants.

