### Eligibility criteria

Couples are eligible for the current study based on the following inclusion criteria: (1) both members were assigned male at birth and currently identify as men; (2) both members are at least 18 years old, and at least one member of the dyad is aged 18–29; (3) both partners consider the other a main or primary partner (defined for participants as “…someone you feel committed to above anyone else. This would be someone you call your boyfriend, partner, or significant other”); (4) the couple endorses oral or anal sex with one another in the last 90 days; (5) at least one member of the couple reports having condomless anal sex with a known serodiscordant or unknown serostatus main partner or with any casual sexual partner; (6) both read and speak English at an eighth-grade level or better; (7) both are able to make it to the study site on six separate occasions (one visit to complete the baseline, four visits for intervention sessions, and one final visit for the 12-month follow-up); (8) both partners agree to having intervention sessions audio-recorded for training and analysis. Note that inclusion criterion #7 was loosened after the onset of the COVID-19 pandemic, as described below.

Couples are considered ineligible if study staff ascertain inconsistencies between information provided by participants in the eligibility screener and the baseline assessment, if issues arise that could potentially hinder participation (e.g., language barriers, intoxication), if both individuals are not able to consistently travel to the study site for the duration of the intervention (before the onset of the COVID-19 pandemic), or if there is imminent risk for harm due to intimate partner violence. If either member of the dyad reports intimate partner violence, study staff complete individual, private check-ins to assess their safety and provide resources. If an individual reports that they do not feel safe, they do not continue in the study.

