Second, the onset of the COVID-19 pandemic in March 2020 spurred us to develop remote protocols for all study activities in order to ensure the safety of our participants and staff. Given that we were already in the process of evaluating an online version of 2GETHER [30], the adaptation of the current protocol was relatively straightforward. In the online version of 2GETHER, all sessions are completed via videoconference (e.g., Zoom). Similar to the protocol described above for couples participating in groups of 1, couples are emailed links to self-paced, narrated videos of the didactic content 1 week prior to each of the group sessions, and group sessions focus on content review and discussion. The protocols for sessions 3 and 4 were not altered for online administration, except that they are now conducted remotely via videoconference. With regard to baseline and 12-month follow-up assessments (other interim time points were already completed remotely), we have made several protocol changes to allow for remote data collection. Participants are sent links to their self-report surveys, hosted via REDCap. Couples are also provided instructions for self-recording their couple communication task via Zoom. Finally, participants are mailed STI testing supplies from Molecular Testing Labs® for self-collection of specimens. Participants ship specimens back to the lab, the lab provides study staff with test results, and study staff communicate results to participants. We experienced a lag between the onset of the pandemic in March and the establishment of an agreement with Molecular Testing Labs® in July 2020. Participants scheduled for a baseline or 12-month assessment during this time period completed all assessment components except for STI testing.

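### The primary STI test is worded as a baseline-to-12-month contrast without naming arm or strata, so it does not match the between-arm hypothesis; depending on the layout it tests change over time or loses about half its power

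*Protocol article*

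**What the plan says.** H1, under Trial objectives and hypotheses, states that "we will observe greater reductions in indicators of HIV risk at 12 months post-intervention among participants randomized to 2GETHER relative to control", and lists "urethral and rectal Chlamydia and Gonorrhea infections" among the primary outcomes. That is a claim about two arms.

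Under Analyses of primary aims, the whole description of the STI analysis is one sentence: CMH "tests of two independent binomial proportions will be used to detect differences in the STI prevalence rates, our primary biological outcome, from baseline to 12-month" assessment. The tested factor and the strata are not named. For the behavioral outcome, the same section does say how treatment enters: as a dyad-level predictor of intercept and slope. Later in the section, mediators are to be tested for "significant differences between the two study arms on the primary outcomes".

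Under Study assessments and Table 1, biological STI testing takes place only at baseline and 12 months, in the same participants. Table 1 calls the outcome STI incidence; the analysis sentence speaks of prevalence.

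**The concern.** A CMH test has one two-level factor, one binary outcome and a set of strata, and its null depends on which variable plays which part. The sentence gives only a time contrast, "our primary biological outcome, from baseline to 12-month follow-up", which is not H1's contrast.

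The sentence also pulls against itself. If the two proportions are the two visits, they are paired and not independent. If they are the two arms, the phrase about baseline to 12 months has no defined role. A CMH test does not test an arm-by-time interaction, so no layout fits every word and also tests a differential reduction.

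Two things are at stake. On the literal layout, a change common to both arms could be reported as a positive primary biomedical result. On another natural layout, a true difference at 12 months would often be missed. A choice that matters this much for a primary outcome should not be left open until the data are seen.

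**Working it through.** **The plan's own power figure.** The power analysis gives 0.89 (medium effect) and 0.99 (large effect) for 125 dyads with within-couple correlation 0.5. Assume two-sided 5% and standardized differences of 0.5 and 0.8, since the article states neither. For a two-arm cluster design with J dyads of size n, the noncentrality is sqrt(J·d² / (4·(ICC + (1 − ICC)/n))) with J − 2 degrees of freedom.
- d = 0.5: sqrt(125 × 0.25 / (4 × 0.75)) = 3.23, power 0.893.
- d = 0.8: sqrt(125 × 0.64 / (4 × 0.75)) = 5.16, power 0.999.

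The figure reproduces, but it is for a difference in means. No power is stated for the STI test.

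**Inputs for the STI test.** 126 people per arm (125 dyads planned, 128 randomized). Two-sided 5% and no continuity correction are assumed. Prevalences are also assumed: 10–20% at baseline, 3–20% at 12 months.

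**Layouts.**
- A: visit by STI, stratified by arm (literal).
- B: arm by STI, stratified by visit.
- C: arm by 12-month STI, stratified by baseline STI.
- D: arm by 12-month STI, unstratified.

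**Formula.** CMH = (Σ(a − E))² / ΣV, with E = n₁m/N and V = n₁n₂m(N − m) / (N²(N − 1)) in each stratum. With n people on each side, a true difference δ shifts a − E by nδ/2 in expectation, and V ≈ n·p̄(1 − p̄)/2. Approximate power is Φ(z − 1.96).

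**By hand.**
- A, both arms 15% to 10%: shift 2 × 126 × 0.05/2 = 6.3; V = 2 × 126 × 0.125 × 0.875/2 = 13.78; z = 1.70; rejects 0.40.
- A, both arms 20% to 10%: shift 12.6; V = 2 × 126 × 0.15 × 0.85/2 = 16.07; z = 3.14; rejects 0.88.
- D, 15% versus 5%: shift 126 × 0.10/2 = 6.3; V = 126 × 0.10 × 0.90/2 = 5.67; z = 2.65; power 0.75.
- B, same truth: the shift is still 6.3, because the baseline stratum adds none, but it adds variance 126 × 0.15 × 0.85/2 = 8.03; V = 13.70; z = 1.70; power 0.40.

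**Simulation** (4,000 trials per row, all participants independent), rejection rates:

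| Truth | A | B | C | D |
|---|---|---|---|---|
| Both arms 15% to 10% | 0.40 | 0.05 | 0.05 | 0.05 |
| Both arms 10% to 5% | 0.58 | 0.05 | 0.05 | 0.05 |
| Both arms 15% to 7% | 0.83 | 0.05 | 0.05 | 0.05 |
| Both arms 20% to 10% | 0.90 | 0.05 | 0.05 | 0.05 |
| Control stays 15%, 2GETHER 5% | 0.40 | 0.40 | 0.76 | 0.77 |
| Control stays 20%, 2GETHER 10% | 0.30 | 0.32 | 0.60 | 0.60 |
| Control stays 20%, 2GETHER 8% | 0.43 | 0.43 | 0.80 | 0.80 |
| Control stays 10%, 2GETHER 3% | 0.30 | 0.30 | 0.63 | 0.64 |

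Layout A also misses opposite trends. With 128 per arm, 2GETHER going from 15% to 10% and control from 15% to 20%, A rejects in 5% of trials and C in 61%.

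With a latent couple correlation of 0.3 and a correlation over time of 0.2, A still rejects 0.40–0.88 under a shared fall. The size of B, C and D rises to about 0.06–0.09, because a plain CMH test ignores couples.

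**The case against.** The strongest reply is that arm is plainly meant. The only two independent groups in the design are the arms. H1, the power analysis, the mediation paragraph and the Discussion all speak of differences between arms or conditions. Nothing says that a pooled fall would count as a primary result. Layout C is an available reading: it fits two independent proportions, explains why a stratified test was named, and loses no power. This stands as evidence of intent, so the sentence is ambiguous and should not be read as a settled decision to test time.

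A reader might infer that the test has the wrong null on every reading. The article does not support that. Under randomization the expected baseline difference is zero, so layout B keeps the equal-arms null and about 5% size with independent data; its fault is dilution. Layout C tests equality of the arms at 12 months directly.

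A reader might also infer that a shared fall is to be expected. The article supports this only weakly. The criterion that "at least one member of the couple reports having condomless anal sex with a known serodiscordant or unknown serostatus main partner" (or any casual partner) carries no time window and needs only one partner. The statement that "the lab provides study staff with test results, and study staff communicate results to participants" describes the mailed kits brought in after the pandemic began. How many participants had the pandemic fall between their two tests is not given.

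Finally, a condensed article may leave factor and strata to the full protocol. That would answer a silent article, but this one names a contrast, and the contrast is not H1's.

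**Conclusion.** The point holds as a mismatch between the stated contrast and H1, together with a factor and strata that are not fixed. The intended factor is probably arm.

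The size depends on the layout. Literally followed, the test would be significant in about 40–90% of trials when both arms fall equally by the assumed amounts. With visit as the stratum, power is about half that of a 12-month comparison. With baseline STI as the stratum, neither problem arises.

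The 40–90% range rests on three assumptions together: the literal layout, baseline prevalence of 10–20%, and a shared fall of 5 to 10 percentage points. It is not a forecast for this trial, and the article does not show that a false positive result is likely. The loss of power rests on the assumed prevalences only, given that layout.

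**What to change.** Replace the sentence with one that fixes the contrast, for example: the primary biomedical analysis compares the proportion positive for any urethral or rectal Chlamydia or Gonorrhea at 12 months between 2GETHER and control, with baseline STI status as stratum or covariate; the null hypothesis is no difference between arms at 12 months. A GEE or mixed logistic model with arm and baseline STI is preferable to a plain CMH test, because it also respects the nesting of partners in couples. Report change from baseline within each arm descriptively only.

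The cost is one sentence. It uses data already in the schedule and needs no further participants or visits. The article describes follow-up as ongoing, so the wording could be settled before the 12-month comparison is made. The small downside is that participants whose baseline fell in the March–July 2020 gap have no baseline STI test and need a stated handling, such as a missing category. A fall seen in both arms could no longer be presented as the primary STI result.

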## Method

We are conducting an attention-matched RCT to test the efficacy of 2GETHER relative to a control condition based on a well-validated positive affect enhancement program [38]. We selected a highly active and attention-matched control condition that is not theoretically linked to HIV risk behaviors. We aim to randomize 200 dyads (individual *N* = 400) to the 2GETHER intervention or control, and we will examine primary and secondary outcomes at 12 months post-intervention, with interim follow-up at 3, 6, and 9 months post-intervention. There were no restrictions regarding receipt of concomitant care during the trial.

The primary HIV risk behavioral outcome will be the occurrence of condomless anal sex acts with serodiscordant or unknown status partners (all casual sex partners will be considered unknown status), and we will account for the reduced risk of condomless anal sex in the context of PrEP use and undetectable viral load (e.g., condomless sex while one has an undetectable viral load may be considered no risk). The primary biomedical outcome will be STI incidence (i.e., urethral/rectal Chlamydia and Gonorrhea), a robust biological indicator of HIV risk. Primary dyadic outcomes will be partner relationship agreement concordance and agreement breaks. Secondary HIV-related outcomes will be indicators of engagement in the HIV continua of prevention and care, including HIV testing (HIV-negative and unknown status participants) and antiretroviral therapy adherence for HIV-positive participants. Exploratory outcomes will be PrEP uptake and adherence (for HIV-negative participants) and viral load (for HIV-positive participants). We will test for dose effects and decay in effects over time, and we will examine relationship functioning as mediators of change in HIV transmission risk. Unless otherwise noted, all outcomes will be measured at the individual level (not couple-level). This is advantageous because HIV risk may also occur with partners outside the relationship. Also, relationships may dissolve during the follow-up period, so measuring individual-level outcomes allows us to examine the effects of 2GETHER behaviors after relationship dissolution. 

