### Randomization to the treatment arm

The original plan for randomizing participants was to randomize each couple to either the active or control condition immediately after both members of the dyad completed the baseline assessment using a stratified randomization scheme within blocks of four. After the trial launch in August 2017, we quickly encountered substantial difficulty in randomizing at the couple level; because the first two sessions of the interventions occur in groups, a large enough number of couples would need to complete baseline within the same timeframe, and these couples’ schedules would all need to align in order to convene group sessions. Because of this, we altered the randomization strategy to randomize at the group level. To achieve this, each couple provides their availability for a set of pre-scheduled group sessions occurring over the subsequent 3 months. Once at least two couples sign up for a group session (six couples maximum), all couples within that group are randomized to the active or control condition. All couples must attend their first group session within 3 months of completing their baseline assessment. Participants who do not attend their first session within 3 months are required to re-complete their baseline assessment; otherwise, they are no longer eligible to be enrolled.

To randomize at a group level, we adopted a more flexible covariate-adaptive randomization method known as Minimization [40, 41] on January 16, 2018, after 10 couples had been randomized using the prior approach. Minimization effectively addresses the scheduling difficulties inherent in couple-level block randomization by allowing sequentially recruited clusters of couples (e.g., 4–12 individuals) to be treated as single units, while offsetting imbalance in both individual- and couple-level prognostic variables [42]. Compared to stratification, Minimization can handle a larger number of prognostic factors and is more efficient in controlling imbalance in baseline variables than simple or restricted randomization [43]. In this trial, we set the biasing probability to 0.80 and used the range as the metric of imbalance in the minimization functioning.

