### Analytic plan

#### Power analysis

At the onset of this trial, we aimed to randomize 200 dyads (*N* = 400) to the active or control condition and powered our trial based on that enrollment goal. We experienced various challenges to attaining this recruitment goal (primarily those described in the preceding section related to scheduling couples into group sessions and challenges during the COVID-19 pandemic), so we adjusted our recruitment goal based on a second power analysis. This power analysis was conducted using WebPower in R for a cluster randomized trial with two arms. This method allowed us to account for the similarity between members of the same couple. We assumed a conservative intra-class correlation between members of the same couple of 0.5 for the purpose of calculating power. With an adjusted goal of randomizing 125 dyads (*N* = 250), power for the present study will be 0.89 to detect a medium-sized effect and 0.99 to detect a large effect for the differences between the two study arms.

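### The primary STI outcome is tested as if participants were independent, although partners always share an arm; at the protocol's assumed couple ICC of 0.5, a nominal 5% test could reach about 11%

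*Protocol article*

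**What the plan says.** All references are to the protocol article.

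- **Status of the outcome.** The Method section states: "The primary biomedical outcome will be STI incidence". It adds that outcomes are measured on individuals unless otherwise noted, so each couple supplies two STI results.
- **Planned test.** Analyses of primary aims assigns this outcome to Cochran-Mantel-Haenszel "tests of two independent binomial proportions will be used to detect differences in the STI prevalence rates". No term or correction for couple or group is mentioned.
- **Other outcomes.** The same section then turns to the behavioral primary outcome and the secondary outcomes. It gives these multilevel growth models, for the stated reason that dyadic data are nested.
- **Power.** The Power analysis section says: "This power analysis was conducted using WebPower in R for a cluster randomized trial with two arms". It continues: "We assumed a conservative intra-class correlation between members of the same couple of 0.5 for the purpose of calculating power".
- **Unit of randomization.** Randomization to the treatment arm explains that the first 10 couples were allocated under a couple-level scheme. From January 2018, once two to six couples had signed up for a session, "all couples within that group are randomized to the active or control condition". Protocol changes after trial launch later allowed a couple to be randomized as a group of one.

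**The concern.** A test for independent proportions takes its variance from the number of people. Here partners can infect each other, share an arm by design, and in most grouped sessions share it with other couples too. If their results are positively correlated, the effective sample is smaller than the number of people. The test then rejects too often, and the matching confidence interval is too narrow. The error is anti-conservative and falls on the only laboratory-measured primary outcome.

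The protocol is also inconsistent with itself. It recognizes couple clustering when it claims power and when it models the other outcomes, and leaves it out for this one test.

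**Working it through.** **Inputs from the article.** 125 couples in the power calculation, 2 people per couple, couple ICC 0.5, stated power 0.89 (medium effect) and 0.99 (large effect); 128 couples randomized; groups of 2 to 6 couples (4 to 12 people).

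**Assumptions.** Alpha is not stated; two-sided 5% is assumed. Medium and large are taken as standardized differences of 0.5 and 0.8. STI prevalence is not given; 5% to 20% is used. No STI-specific ICC and no group-level ICC is given.

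**Step 1: reproduce the stated power.** For a two-arm cluster-randomized comparison with J clusters of n people, the noncentrality is λ = √[J·f² / (4·ICC + 4(1−ICC)/n)], on J−2 degrees of freedom.
- Denominator: 4(0.5) + 4(0.5)/2 = 3.
- Medium: λ = √(125 × 0.25 / 3) = 3.23, power 0.893 (stated 0.89).
- Large: λ = √(125 × 0.64 / 3) = 5.16, power 0.999 (stated 0.99).
- A one-sided test would give 0.941 for the medium effect, and ignoring clustering would give 0.977. Neither matches 0.89.

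The stated power therefore belongs to a two-sided 5% analysis that accounts for couples, which the planned STI test is not.

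**Step 2: true size of the independence test, couples only.** The design effect is DEFF = 1 + (2−1)·ICC, and the true size is 2[1 − Φ(1.96/√DEFF)].

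| Couple ICC | DEFF | True size |
|---|---|---|
| 0.1 | 1.1 | 0.062 |
| 0.2 | 1.2 | 0.074 |
| 0.3 | 1.3 | 0.086 |
| 0.5 | 1.5 | 0.110 |

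At ICC 0.5 intervals should be √1.5 = 1.22 times as wide.

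**Step 3: simulation under the null.** One-stratum CMH statistic, 64 couples per arm, couple ICC 0.5, prevalence 5% to 20%.
- No continuity correction, complete data: 0.105 to 0.112.
- No correction, 20% of results missing at random: 0.095 to 0.102.
- Continuity correction, complete data: 0.062 to 0.084.
- A couple-level t test on the same complete data: 0.047 to 0.051.

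A CMH test stratified by baseline STI (125 couples, prevalence 5% to 15%, no missing results) gave 0.105 to 0.111 at ICC 0.5 and 0.076 to 0.086 at ICC 0.3. Stratifying by baseline STI does not remove the problem.

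**Step 4: can another stratification rescue the test?** No. Arm does not vary within a couple or within a randomized group, so strata defined by either carry no information on treatment.

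**Step 5: group randomization, illustration only.** With m people per group, DEFF = 1 + ICC(couple) + (m−2)·ICC(group). At couple ICC 0.5 and an assumed group ICC of 0.01 to 0.05, the size is 0.112 to 0.121 for m = 4, 0.117 to 0.144 for m = 8, and 0.121 to 0.166 for m = 12. The group ICC is an assumption, so these figures show only the direction and a possible range.

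**The case against.** The strongest objection concerns size. A reader might infer that the error rate is simply doubled. The article does not support that. Its ICC of 0.5 is a generic planning value, described as conservative, and not an estimate for STI. At 10% prevalence it implies that the partner of a positive participant is positive with probability 0.10 + 0.5 × 0.90 = 0.55. Couples may also separate during follow-up, which would tend to weaken the correlation at 12 months. With an ICC of 0.3 and a continuity correction, the simulated size is 0.043 to 0.065, so there may be little net inflation. This objection stands as a limit on the size. It does not make the test valid: the correction is conservative under independence (0.020 to 0.034 in the same simulation) and only offsets the clustering by accident.

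Group randomization has no stated ICC. It does not affect the first 10 couples or couples randomized alone, and the number randomized alone is not given. Its contribution cannot be sized.

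Two further readings are tempting and should not be pressed.
- A reader might infer that the test treats the same people's baseline and 12-month results as independent samples. The wording is ambiguous, but the two proportions are most naturally the two arms.
- A reader might infer that everyone affected by the 2020 specimen gap, who "completed all assessment components except for STI testing", is dropped from the test. The article names neither a stratifier nor a missing-data rule for this outcome, and such a rule commonly sits in the analysis plan, which is not at hand.

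**Conclusion.** The concern holds: the named test is wrong for the design as written, and this does not depend on any assumed correlation. Both partners contribute results, they always share an arm, and nothing in the article adjusts the STI test for couple or group.

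The size of the error is conditional. If the STI correlation within couples is the protocol's own 0.5 and no continuity correction is used, a nominal two-sided 5% test has a true size of up to about 11%, and 95% intervals should be about 22% wider. At 0.1 to 0.3 the size is about 6% to 9%. A continuity correction or missing results lower these figures; a group effect would raise them by an amount that cannot be determined from the article. All figures assume a two-sided 5% level, which is not stated but is the one that reproduces the stated power.

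**What to change.** Replace the test with a between-arm comparison of 12-month STI positivity that accounts for clustering on the randomized unit: the group, or the couple where it was randomized singly. Any of these would do, provided one is named in advance:
- GEE logistic regression with cluster-robust standard errors and a small-sample correction;
- mixed-effects logistic regression with small-sample-corrected cluster-robust inference;
- a cluster-adjusted CMH test.

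Adjust for baseline STI status and the other minimization factors (couple age discordance and couple HIV status). State the alpha level and sidedness in the same paragraph.

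The cost is one paragraph of wording, slightly more analysis work and a wider confidence interval. No new data are needed.
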